### Assessment instruments

#### a) Clinical variables

1 Depressive symptoms: measured by the Hamilton Depression Rating Scale of 17 items (HDRS-17) [44,52]. 3. Manic symptoms: measured by the Young Mania Rating Scale (YMRS) [45]. 4. Hamilton Anxiety Scale HAM-A [47]. 5. Clinical Global Impression Scale modified for bipolar disorder (CGI-BP) [46]. 6. Adherence to treatment: Good (according to information from the patient, family and blood drug levels), Bad (if none of the above criteria are met) or Average (only if it meets one or two criteria). 7. Clinical outcome: new mood episodes, serious adverse events (including suicidal ideation, suicide and hospitalization).

#### b) Cognitive variables

##### General cognition

Sustained attention (Continuous Performance Test, [53]). The test provides the following measures: correct responses, errors of omission (not responding when the stimulus appears) and commission errors (responding without the letter stimulus appearance).Selective attention (Stroop Test, [48]). Requires the subject to be able to suppress irrelevant response. When the name of a color (e.g., “blue,” “green,” or “red”) is printed in a color not denoted by the name (e.g., the word “red” printed in blue ink instead of red ink), naming the color of the word takes longer and is more prone to errors than when the color of the ink matches the name of the color [54].Working memory. 1. Subtest from the Weschler Adult Intelligence Scale [55]. A sequence from 2 to 8 digits or a list of words have to be repeated in reverse or random order of presentation.Executive functions: 1. Wisconsin Card Sorting Task [56]. Participants have to sort the cards according to different criteria that vary throughout the test (perseverative errors and completed categories are the dependent variables).

#### c) Social cognition

The recognition of emotions through the face is measured with the Face Emotion Identification Task and Face Emotion Discrimination Task (FEIT and FEDT respectively, [57]). The FET scale includes 19 photographs of faces expressing one of the six basic emotions (happy, sad, angry, scared, shocked or embarrassed). The task is to identify the patient’s emotion expressed in each. The FEDT includes 30 pairs of faces and the subject must determine if both sides show the same or different emotion.

#### d) Mindfulness

Five Factors Questionnaire Mindfulness (FFMQ, [58]) 39 items assessing five mindfulness facets: observing, describing, acting with awareness, equanimity and no reactivity. Each item is scored on a Likert scale ranging from 1 (never) to 5 (very often). A high internal consistency and high predictive validity have been shown [58] and it has been uvalidated in Spanish [59].

#### e) Functioning

Measured with the Functioning Assessment Short Test (FAST, [49]), which measures the degree of difficulty found by the patient in the following areas: autonomy, occupational functioning, cognitive functioning, finances, relationships and leisure.

#### f) Biomarkers: serum analysis of BDNF

### Data analysis

An exploratory study of all collected variables identifies possible outliers and errors. The descriptive analyses of qualitative variables are expressed as frequencies and percentages and quantitative variables as mean, standard deviation, median and interquartile range. Analysis is performed by intention to treat. Comparison of qualitative variables between the intervention groups or between other factors of segmentation is by means of Chi 2 or Fisher ‘s exact test. For quantitative variables, the T-test, Mann -Whitney or Kruskal –Wallis and ANOVA are applied, depending on the normality of the variable (tested by Kolmogorov -Smirnov - Lilliefords). The change analyses along the track of the primary and secondary outcome variables are performed using a General Linear Model (ANOVA with repeated measures). Regression models are extracted to identify prognostic factors for the efficacy variables. The statistical package SPSS 18.0 is used in all tests and a bilateral level of p < 0.05 is considered statistically significant.

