## Methods/design

This is a parallel 3-group, multicenter, prospective, randomized; single-blind (evaluator) controlled pilot trial, with a 4 month follow-up post-intervention. Patients diagnosed with bipolar disorder (BD) according to DSM −5 criteria for mild depression or subsyndromal depressive symptoms are assigned to one of the following 3 treatment groups: 1) psychopharmacological treatment *plus* Mindfulness Based Cognitive Therapy (MBCT); 2) psychopharmacological treatment *plus* a brief, structured group psychoeducation; 3) treatment as usual (TAU), defined as standard psychiatric care with standard pharmacologic treatment. After written informed consent is signed, patients meeting the inclusion criteria are randomized (2:2:1 ratio) through a Random Allocation Software. All three groups are assessed at baseline (t0), immediately after completing the program (t1; 8 weeks) and at follow-up six months after randomization. The assessments include the following variables: depression, manic and anxiety symptoms, general and social cognition, global functioning, BDNF, and other clinical variables. The evaluator who will collect the biomarkers and the clinical and psychometric data will be blind to allocation of treatment. The interrater variability between all researchers will be checked.

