### Subjects

One hundred and forty bipolar out-patients with persistent mild/subsyndromal depressive symptoms will be recruited from Mental Health Centers as well as Private Psychiatric Clinics and Bipolar Patient Associations via announcements or physician referral. The study will be conducted in La Paz University Hospital (Madrid) and the Santiago Apóstol University Hospital (Vitoria).

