### Inclusion criteria

1-Age: 18–60 years; 2 – BD type I or II, in clinical remission of acute mood episode at least in the three months prior to study; 3 - Having experienced an acute affective episode in the past 3 years, 4 - Having suffered at least two lifetime depressive episodes. 5- Monotherapy or combination with a mood stabilizer (lithium, valproate, carbamazepine or lamotrigine) at optimal doses (i.e., in serum levels within the therapeutic range: 0.6-1.2 mEq/L for lithium, 50–100 ug/mL for valproate, and 5–12 mcg/mL for carbamazepine), or quetiapine monotherapy or in combination with the aforementioned stabilizers, or any oral atypical antipsychotic in combination with an antidepressant; 6.- Hamilton Depression Rating Scale [HDRS]–17 [44] score ≥ 8 and ≤ 19 and Young Mania Rating Scale [YMRS; 49] score <8; 7 - Being able to understand and comply with the requirements of the trial, 8 - Written consent to participate in the study.

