### Primary outcome measures

Primary endpoint of the study is given by changes in the overall score of the Hamilton Rating Scale for Depression (HDRS [44]), from baseline (V0) to week 8 (v1) for each of the treatment groups.

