### Intervention

MBCT program will be conducted in HULP by two experienced therapists with recognized expertise in Mindfulness based stress reduction (MBSR), MBCT and narrative psychotherapy. Both therapists will train two therapists from Vitoria with expertise in cognitive therapy and MBSR. The MBCT program consists of 8 weekly sessions of 90 minutes and will be performed in groups of approximately 10–15 patients. All therapy sessions will be audio recorded to be discussed and analyzed by the treatment team, in order to standardize the intervention. Treatment fidelity will be also assessed using the Mindfulness- based Cognitive Therapy Adherence Scale (MBCT-AS; [50]), which assesses the key constructs of MBCT during group sessions.

Psychoeducation program will be held in groups of 10 to 15 patients in 90-minute weekly sessions led by two therapists blind to the clinical and cognitive evaluation. The specific program of 8 sessions addresses disease awareness, adherence to treatment and early detection of prodromal symptoms. Homework will also be included. The program is based on the Psychoeducation Manual for Bipolar Disorder [51]. Attendance to at least 80% of the sessions of both interventions will be required to be considered complete.

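### The article fixes an unadjusted-change analysis for HDRS and leaves open whether a normality pre-test also picks the efficacy test; name one baseline-adjusted model in advance

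*Protocol article*

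**What the plan says.** Three parts of the protocol article bear on this.

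- **Endpoint.** Primary outcome measures defines the primary endpoint as the change in HDRS total "from baseline (V0) to week 8 (v1) for each of the treatment groups".
- **Model.** Data analysis states: "The change analyses along the track of the primary and secondary outcome variables are performed using a General Linear Model", specified in brackets as repeated-measures ANOVA. No covariate is named. Regression appears only as a search for prognostic factors, not as adjustment of the treatment comparison.
- **Choice of test.** The sentence before the model lists the t-test, Mann-Whitney, Kruskal-Wallis and ANOVA for quantitative variables. These "are applied, depending on the normality of the variable", as judged by a Kolmogorov-Smirnov-Lilliefors test. It does not say whether week-8 HDRS or the HDRS change falls under this rule, or which result prevails if both routes are used.

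For scale: Subjects plans "One hundred and forty bipolar out-patients with persistent mild/subsyndromal depressive symptoms", Methods/design has them "randomized (2:2:1 ratio) through a Random Allocation Software", and Data analysis says "a bilateral level of p < 0.05 is considered statistically significant". The entry range for HDRS is "score ≥ 8 and ≤ 19 and Young Mania Rating Scale [YMRS; 49] score <8".

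**The concern.** Repeated-measures ANOVA treats baseline HDRS as a response. For baseline and week 8, its group-by-time test is the same as comparing raw changes between arms. That fixes the coefficient of baseline at 1, whatever the data show. If the true slope is below 1, the estimate carries needless noise, and part of any chance difference between arms at baseline stays in it.

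The pre-test sentence raises a second issue. A t-test or ANOVA addresses a difference in means; a rank test addresses an ordering of distributions and yields no adjusted mean difference. If the rule reaches the efficacy endpoints, the reported quantity is settled only once the data are seen. The Discussion section says the trial is to supply preliminary effect size estimates and concedes that sample size may be a limitation. Both make a single, reasonably precise mean difference worth fixing in advance.

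**Working it through.** **Inputs from the article.** N = 140 at 2:2:1 gives 56:56:28. The main comparison (Abstract) is MBCT versus psychoeducation, 56 v 56, so N = 112 for that contrast. Alpha is 0.05 two-sided. Baseline HDRS is an integer from 8 to 19. The article states no effect size, SD, baseline-to-week-8 correlation, power or dropout, so there is no figure to reproduce, and everything below rests on assumed ranges.

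**1. Precision of adjusted versus unadjusted change.** Let s0 and s1 be the SDs at baseline and week 8, r their correlation and b = r·s1/s0 the slope.

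Var(ANCOVA)/Var(change) = s1²(1 − r²) / (s0² + s1² − 2·r·s0·s1)

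The cost of two covariates (baseline and site) is a factor of about 1 + 2/(N − 5) = 1 + 2/107 = 1.019.

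Example with s0 = 3 and s1 = 5:

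| r | slope b | ratio | with cost |
|---|---|---|---|
| 0.3 | 0.50 | 22.75/25 = 0.91 | 0.927 |
| 0.4 | 0.67 | 21/22 = 0.955 | 0.972 |
| 0.5 | 0.83 | 18.75/19 = 0.987 | 1.005 |
| 0.6 | 1.00 | 16/16 = 1.000 | 1.019 |

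**2. Allowing for the entry range.** Baseline was drawn from normal populations with assumed mean/SD of 12/4, 10/4 and 8/5, rounded and restricted to 8-19. Week 8 had the same population SD, with unrestricted correlations of 0.3-0.7. Selection on baseline leaves the slope at 0.3-0.7 and lowers the correlation. After the covariate cost the ratios run from about 0.79 (slope 0.3) to 0.96 (slope 0.7), a variance reduction of about 4-21%. At slope 1 the ratio is 1.02.

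The gain also depends on the residual SD e, since the ratio equals e²/(e² + (1 − b)²·s0²). With e = 5, s0 = 3 and b = 0.7 it is 25/(25 + 0.09·9) = 0.969, or 0.987 with cost. A noisier week-8 score therefore leaves less to gain.

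**3. What this means for power.** At 56 v 56 and a standardised change difference of 0.5 (assumed), power is 75.4% for unadjusted change. It becomes 77.5% at a ratio of 0.95, 81.9% at 0.85 and 84.1% at 0.80.

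**4. Chance baseline imbalance.** With s0 = 2.9, one standard error of the baseline difference is 2.9·√(2/56) = 0.55 HDRS points. Unadjusted change carries (1 − b) of it: at b = 0.5, about 0.27 points.

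**5. Site.** Adding site alone multiplies the variance by 1.01 if site explains nothing and by 0.96 if it explains 5% (assumed).

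**6. The normality pre-test on the HDRS change.** Lilliefors rejection at 0.05 for an exactly normal change rounded to integers, simulated:

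| SD of change | n = 56 | n = 140 |
|---|---|---|
| 3 | 42% | 92% |
| 4 | 23% | 61% |
| 6 | 12% | 28% |

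The result thus turns on rounding, SD and sample size, with no real departure from normality in the underlying scores.

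**The case against.** **The article is condensed and the trial calls itself a pilot.** Covariate lists are commonly left to an analysis plan, and unadjusted change is unbiased under randomisation. Both are fair. But the article does not leave the method open: it names repeated-measures ANOVA for the outcome variables. The point concerns the efficiency of that choice, not bias.

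**The pre-test may not touch efficacy at all.** The sentence follows one on comparing qualitative variables between groups or other segments, and the model sentence carries no normality condition. It can be read as general group description. This stands, so the pre-test is an ambiguity to resolve and not a proven flaw of the primary analysis.

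**Stronger readings that the documents do not support:**

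- *The 8-19 range makes the efficacy variable fail the normality test.* That range is an entry criterion and limits baseline only; Secondary endpoints foresees scores of 20 or more later. Rejection of 54-93% at n = 56 and 99-100% at n = 140 applies to baseline HDRS, which is not an efficacy endpoint.
- *The p-value loses its nominal error rate.* A simulation of the two-stage rule under the null (56 v 56, 5,000 runs, three assumed settings) gave rejection of 4.8-5.3% for change and 4.3-5.0% for week-8 HDRS, although the test was switched in 36-77% of runs.
- *Unadjusted change needs 25-54% more patients.* That follows from the ratio (1 + r)/2, which is 0.80-0.65 for r = 0.6-0.3, and requires equal SDs at both visits. Entry selection restricts the baseline SD only, so equality is doubtful.
- *Site matters because therapists differ.* Intervention does say "Both therapists will train two therapists from Vitoria with expertise in cognitive therapy and MBSR", but that same cross-site training, with recorded sessions, aims at a standard delivery. No site effect is given, and the gain in step 5 is small.

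**Conclusion.** The point holds in limited form. The article fixes an unadjusted-change analysis for its primary and secondary outcomes although baseline values are collected. A baseline-adjusted model is likely to be more precise, with about 4-21% less variance at assumed slopes of 0.3-0.7, and removes the effect of chance baseline imbalance. The benefit is not guaranteed: it shrinks with a larger residual SD and disappears at a slope near 1, where the loss is at most about 2%. None of these slopes or SDs can be checked against the article.

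On the choice of test, the article must say whether the normality rule reaches the efficacy endpoints. If it does, the estimand would depend on a pre-test that rounding alone can trigger in roughly one sample of 56 in eight (SD 6) to two in five (SD 3). That is a problem of interpretation; an inflated type I error is not shown.

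**What to change.** In Data analysis:

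1. Name one primary model in advance: week-8 HDRS on arm and baseline HDRS, as ANCOVA or as a mixed model with baseline as a covariate. Report the adjusted mean difference with its confidence interval. Site may be added as a minor term.
2. Use the same form for each continuous secondary endpoint, with that endpoint's own baseline as covariate.
3. State that the normality pre-test does not apply to efficacy endpoints. Keep rank-based results as a named sensitivity analysis.
4. Describe the expected gain in precision as likely but dependent on the slope.

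The cost is analysis wording only, since baseline values and site are already recorded. If an analysis plan already specifies such a model, the article's wording only needs to be aligned with it.

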### Ethical issues

The study is conducted according to local regulations and internationally established principles at the the Helsinki Statement (64° Asamblea General Fortaleza, Brasil, 2013), whilst respecting confidentiality (Data Protection Act 15/99). Protocol was approved by the Clinical Research Ethics Committee of the University Hospital La Paz (Madrid) and the Clinical Research Ethics Committee of the Basque Country.

## Discussion

This study will provide feasibility information and preliminary effect size estimates to inform the effectiveness of adjunctive MBCT, adjunctive group psychoeducation and standard treatment on SS or mild depressive symptoms in BD. It is of interest to researchers involved in the development of new approaches to the treatment of residual affective symptoms and its negative impact in the course of illness. It can also provide information on variations of BDNF in the different treatment arms and on neuropsychological measures, which might suggest mechanisms of action and differences among treatments.

Strengths of the study include targeting a defined sample of bipolar patients with persistent depressive symptoms despite receiving a correct pharmacological treatment. This sample –as reported before- is representative of a high percentage of bipolar out-patients, who remain symptomatic more than one third of the time. The trial protocol was registered before randomization began (ClinicalTrials.gov: NCT02133170 Registered 04/30/2014) and was developed according to good clinical research practice enabling the randomized trial to be conducted with low risk of bias and a high degree of external validity. Both MBCT and psychoeducational interventions will be conducted using manuals and adherence to the treatment manuals will be tested. This makes it possible to implement the interventions in clinical practice, and the two interventions can be assessed in future trials. To standardize the application of MBCT and psychoeducation, specific training and meetings will be held. Specific training also may increase the inter-rater reliability on scales.

Since an 8-week psychoeducational program based in the Barcelona group-structured model has not proved effective neither in depressive symptoms nor in episode prevention, this could be a study weakness. But our objective is to compare MBCT versus an active psychosocial intervention, and this is the best model we could find. Sample size could also be a limitation, as well as the time of follow-up, especially regarding the possible effects on long-term course of BD.

## Abbreviations

ANOVA: Analysis of variance
BD: Bipolar disorder
BDNF: Brain derived neurotrophic factor
CBT: Cognitive behavioral therapy
CGI-BP: Clinical global impression scale modified for bipolar disorder
FAST: Functioning assessment short test
FEDT: Face emotion discrimination task
FEIT: Face emotion identification task
FFMQ: Five factors questionnaire mindfulness
HAM-A: Hamilton anxiety scale HAM-A
HDRS: Hamilton depression rating scale
IPSRT: Interpersonal and social rhythm Therapy
ABIs: Mindfulness and acceptance-based interventions
MBCT: Mindfulness based cognitive therapy
SS: Subsyndromal symptoms
YMRS: Young mania rating scale
